## Abstract

**Objective:**

To assess the feasibility of implementation of a “***SHVASAN***” model for screening and diagnosis of COPD and Asthma at the primary health care level. Methodology: Mixed methods to assess feasibility, including the Delphi technique. Implementation will begin with the training of ASHAs, CHOs, and equipment will be provided for setting up the screening and diagnosis across one rural PHC in Pune district, India. All 35 villages and ASHAs would be screening the population above 30 years of age. And CHOs across all Health and wellness centres (06 + 02 at PHC and one at RH) will diagnose the CRDs. Feasibility would be assessed after one year of the ***SHVASAN*** model implementation. A Delphi study would be conducted to formulate the feasibility dimensions and formulate the feasibility index. Considering feasibility dimensions, qualitative and quantitative data would be collected to assess the feasibility of the model, which includes the population screened by the ASHAs and the number of diagnostic tests conducted at health wellness centers. And focused group discussions, in-depth interviews will be conducted to understand the facilitators and operational challenges of the ***SHVASAN*** implementation.

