### Methodology to measure feasibility index

A feasibility assessment will help determine whether the research is practical, manageable, and likely to achieve the screening and diagnosis of COPD or asthma. Little is known about the feasibility of screening and diagnosing COPD-Asthma in peripheral health care delivery; therefore, to determine the feasibility measure, a unique methodology will be applied. The Delphi Method: Delphi's value for adaptation, promoting feasibility metrics and iterative refinement to connect the evidence-to-practice gaps in primary care (25). The Delphi method is most suitable as it is a structured, iterative process used to gather and refine the opinions of a panel of experts to finalize the feasibility measures, focusing on assessing feasibility (26). Based on the Delphi method output, a feasibility index may be developed at the health and wellness center level. The final dimensions later guide the questionnaire for the qualitative and quantitative data collection.

The Delphi technique seeks to address the following question related to the Feasibility Index of the ***SHVASAN*** model:
(a)Are the proposed dimensions for assessing feasibility appropriate?(b)What suggestions would you have to improve the dimensions? (By adding the new dimension, by deleting the suggested dimensions, or by modifying the dimension)(c)How can the feasibility index be developed based on the given dimensions?(d)How can each component be weighted? (Table 2)The steps for the Delphi technique:

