(a)Draft feasibility dimension and implementation indicators for the ***SHVASAN*** model based on literature review, program guidelines, and field requirements(b)The experts were purposively selected and invited based on their domains and expertise in the field of implementation research, health system and policy researchers, policy implementers, health administrators, public health academics, and pulmonology. A panel of six to eight experts will be targeted to ensure multidisciplinary representation.(c)Sharing of the first round of the Delphi questionnaire/related material with the shortlisted feasibility dimensions, asking them their opinion based on relevance, feasibility dimensions suitability, they will be asked to modify (MO) or keep (KP) the dimension, and share feedback on weights to each feasibility component.(d)Collect and summarize the first feedback using descriptive statistics and synthesis of open-ended responses, if any.(e)Revise, merge, delete, or add items based on the first round(f)A consensus of >95% agreement among the participating experts for retaining the dimension will be considered.(g)An iterative round to share feedback and revised items in the second round of the Delphi technique.(h)Analysis of second round expert feedback to identify consensus and non-consensus items.(i)Finalize the feasibility dimensions and weights to calculate the Index.(j)Final dissemination meeting with Experts

**Table 2 T2:** The proposed feasibility dimension to calculate the index includes.

Feasibility Component	Technical feasibility	Operational feasibility	Resources Feasibility	
Indicators	1. Recruitment rate 2. Quality of Data Collection Procedures 3. Outcome Measures 4. Technical skill in performing the PEFR 5. Suspected cases- referrals from the screened population 6. Technical skill of conducting a spirometry test 7. Correct interpretation and diagnosis	1. Overall stakeholder acceptability (Participant satisfaction Staff satisfaction, Readiness to perform screening and diagnosis techniques) 2. Month-wise percentage of time taken for the ASHAs to complete their target 3. Month-wise percentage of time taken by CHOs for the screening and diagnosis 4. percentage of deviation in the place of conduction (actual vs. deviation) 5. Dropout Rates/Retention Rate	1. Infrastructure to deliver the Model 2. Human resources 3. Cost for equipment Direct Indirect 4. Cost for training 5. Cost per participant	[figure not shown]

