A Feasibility index document tool is being developed using the Delphi technique. That will include feasibility dimensions: Technical, Operational, and Resource- All three dimensions would be measured using study tools. The COPD-Asthma screening questionnaire: Existing pretested and validated questionnaires assessing the risk factors and exposures, such as smoking, use of biomass fuel, family history, quality of life, and medical history, as well as known cases of COPD or Asthma in the eligible population. The Peak exploratory flow rate (PEFR) skills, screening of the population, will help calculate the technical feasibility. That may be reflected through the number of suspected cases, the recruitment rate, the retention rate, and the screening rate.The COPD-Asthma diagnosis proforma: An existing, pretested, and validated proforma will be used to diagnose suspected cases. It will be filled by CHO at HWC. The proforma will document the medical history, symptoms, comorbidities, treatment, and vital clinical measurements such as blood pressure, blood oxygen level, Pulse, etc. Related and other pertinent clinical findings will be noted. A pre- and post-spirometry reading and interpretation in accordance with the NPCDCS 2021 guidelines, the categorization of COPD and asthma will be documented in the same proforma. This will also help calculate the technical feasibility of the diagnosis.The PEFR checklist for skills assessment of ASHAs would be completed by the investigator at two time points: after the training and during field data collection by ASHAs.Spirometry testing activity checklist for the skill assessment during the conduction of the test at HWC.Data Quality Checks
Data collection –for the quantitative data, Quality checks will be conducted while collecting data at the community level. Quality checks would be conducted randomly on at least 5% of the sample.Quality checking for the Peak flow meter skill can be done using the checklist to be filled out by the field senior supervisorsA Spirometry quality checklist will also be filled out every time of the observation.Random quality checking visits will be planned by technical experts for PEFR and Spirometry testing.

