Quantitative - Data will be entered in Microsoft Excel and then imported to SPSS (version 27) for Windows package (IBM SPSS Statistics for Windows, Version 25.0. Armonk, NY: IBM Corp). The proportions of categorical variables of interest (Respondents with COPD-Asthma diagnosis in both PHCs) will be compared using the Chi-Square test. Means of variables of interest (time for symptoms, diagnosis, age, severity of disease) will be compared using the independent t-test. The associations between disease proportion and PEFR and spirometry values will be determined using the chi-square test. A multivariate logistic regression analysis will be carried out to identify significant predictors using PEFR values in implementing PHCs.Qualitative analysis -Data from IDIs and focus group discussions will be transcribed and thematically analyzed, and if required, MaxQDA software may also be used. In-depth interviews and focus group interviews will be transcribed verbatim, checked, and corrected if required. The transcripts will then be thematically analyzed. The transcripts will be independently read to become familiar with the material. The notes on insights and patterns from the transcripts will be derived. Subsequently, participants and/or the guide may engage in discussion to reach a consensus on the content. Coding transcripts using code labels closely linked to the meaning of the quotes, and organizing codes with similar content into groups and themes, would generate initial themes. Groups and initial themes were then presented and discussed with the guide. Then, if suitable, the Normalisation Process Theory (NPT) (27) will be used as a theoretical lens to understand how the implementation of codes and initial themes, organized within the constructs of NPT, were reviewed before being refined and delineated into four main themes. In cases where themes overlap with more than one NPT construct, a best-fit choice will be made. The content will be finalized thematically later.The comparative analysis of data from both PHCs would be done using the chi-square test for characteristics of diagnosed cases. The number of newly diagnosed cases during the study period would be obtained from the Public Health Management Information System (HMIS)Feasibility index - Based on qualitative and quantitative data collection and analysis, the feasibility dimensions will be scored and finalized through Delphi consensus. The feasibility index may be derived from the scores and the assigned weights.

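### The analysis plan has the primary index's dimensions finalised by Delphi after data are analysed, while the methods have them finalised first; the two orders must be reconciled

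*Protocol article*

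**What the plan says.** The Outcomes section makes the feasibility index the primary outcome and commits it to technical, operational and resource feasibility.

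The protocol article describes how the index is built in several places:

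- **Abstract.** Dimensions are the starting point: "Considering feasibility dimensions, qualitative and quantitative data would be collected to assess the feasibility of the model".
- **Methodology to measure feasibility index, opening text.** The index comes from the Delphi ("Based on the Delphi method output, a feasibility index may be developed at the health and wellness center level"), and the Delphi result precedes data collection: "The final dimensions later guide the questionnaire for the qualitative and quantitative data collection".
- **Same section, Delphi steps.** Step (a) drafts the dimensions and indicators for the "model based on literature review, program guidelines, and field requirements". After two rounds of expert feedback, step (i) reads: "Finalize the feasibility dimensions and weights to calculate the Index".
- **Quantitative component, research tools.** "A Feasibility index document tool is being developed using the Delphi technique".
- **Plan for analysis, feasibility index item.** "Based on qualitative and quantitative data collection and analysis, the feasibility dimensions will be scored and finalized through Delphi consensus". The next sentence adds: "The feasibility index may be derived from the scores and the assigned weights".

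**The concern.** The last of these places reverses the order of the others. It puts data collection and analysis first, and the scoring and finalising of dimensions by the panel second.

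This bears directly on the primary outcome. The Delphi questions in the methodology section allow the panel to add, delete or modify dimensions, and the Study design section gives it measurement scoring and data sources as well. Used before results exist, these powers are ordinary instrument development. Used by experts who know which indicators did well and which did badly, they let the results influence the measure by which those results are judged. Nothing in the article says that the index is locked, or that the panel is kept from results, before finalisation.

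**Working it through.** The article gives no figure on this point, so the check sets the texts side by side.

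| Place in the protocol article | When dimensions are finalised | What feeds the finalisation |
|---|---|---|
| Abstract | Before data collection, which takes the dimensions into account | Delphi |
| Methodology, opening text | Before data collection, which the final dimensions guide | Delphi output |
| Methodology, steps (a) to (j) | Step (i), after round 2 | Literature, guidelines, field requirements, expert feedback |
| Quantitative component, research tools | Under development by Delphi; no order stated | Delphi |
| Plan for analysis | After data collection and analysis | Collected and analysed data, then Delphi |

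1. **Can both orders be true?** Not for one Delphi. If final dimensions shape the questionnaires, they exist before the data. If they are finalised on the basis of the data and their analysis, they do not.
2. **Could there be two Delphi exercises?** None of the ten listed steps, (a) to (j), takes study data as an input, and no section describes a further exercise after the data. The only later event listed is a dissemination meeting with the experts at step (j).
3. **Which order fits the rest of the text?** Delphi first. The Study design section also uses the Delphi to settle the intervention package, which makes sense only ahead of implementation.
4. **What is exposed under the literal reading?** The three component headings are named in Table 2, in the research tools text and in the primary outcome. Below them Table 2 lists 7 technical, 5 operational and 5 resource indicators, 7 + 5 + 5 = 17, all labelled as proposed. The choice of indicators and the rules for scoring them are what could move.
5. **What about weights?** The final sentence of the analysis item speaks of weights as assigned. With step (i), this most naturally means weights already set by the end of round 2.

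**The case against.** The strongest reply is that one compressed sentence is being set against a consistent account everywhere else. Scoring has to rest on data and finalising belongs to the Delphi. The sentence may simply have run the two together, meaning that dimensions already finalised by the panel are then scored from the data. The figure showing the sequence and timeline of the study components is not available here and may make that order plain.

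This is plausible, and it limits how firmly one can say what the investigators intend. It does not remove the contradiction. The sentence joins scoring and finalising and bases both on analysed data, and a figure elsewhere would not correct it. Nor is this a detail that a condensed article may leave to a fuller document, since two printed statements disagree and no further document can make both true.

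On the hedge in "The feasibility index may be derived from the scores and the assigned weights", it is fair to answer that the methodology section hedges in the same way and that the Outcomes section does commit to calculating the index. The hedge is therefore a minor point, worth correcting in the same edit.

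A reader might also infer that the panel could reweight the components once results are known. The documents do not say so, for the reason in point 5 of the working, and a calculation that varied the weights would not measure this defect.

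**Conclusion.** The contradiction is real and concerns the sole primary outcome. As written, the analysis text permits changes to indicators and scoring inside three fixed components after results have been seen. That is a stated rule open to bias, not a missing detail. Its size cannot be calculated, because the article gives no component scores, scoring rules or weights.

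The conclusion rests on a literal reading of the analysis sentence and on the absence of any described second Delphi. If the sentence is only loosely worded, the defect is confined to the text, but it still needs correcting because it is the only analysis text for the index.

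Two stronger inferences are not supported:

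- **That almost any data could be made to show feasibility.** The primary outcome is committed in advance to all three components, so a whole component cannot simply be left out without departing from it.
- **That the plan is defective because no index value is labelled feasible.** A condensed article may leave a cut-off to the full protocol or to the Delphi tool, which is still being developed, and the last column of Table 2 is not shown.

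**What to change.** Replace the feasibility index item in the Plan for analysis with text along these lines:

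> *Dimensions, indicators, scoring rules and weights are fixed at the end of Delphi round 2, before implementation results are tabulated or shown to the panel. Only the scores come from study data. The feasibility index will be derived by applying this fixed formula.*

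Give the locked index a version date. If screening has already begun, do not show the panel accumulating results until the index is locked. If a Delphi round after the data really is intended, describe it and state what it may change.

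The cost is a wording change, a dated version of the index, and the loss of freedom to revise the index later. No additional data are needed.

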
### Outcomes

#### Primary outcome

Feasibility of implementing the ***SHVASAN*** model by calculating the feasibility index for the feasibility of ’Screening by Accredited Social Health Activist (ASHAs)and diagnosis by Community Health officers of Asthma and COPD at the primary health care System- A Novel Strategy (***SHVASAN*** model). This will consider technical, operational, and resource feasibility.

#### Secondary outcome

Secondary outcome: Facilitators and operational challenges in the Implementation of the ‘***SHVASAN***’ Model. Prevalence of COPD and Asthma in implementing PHC and in adjuvant adjacent PHC.

## Discussion

***SHVASAN*** builds on the COPD 2021 guidelines by utilizing peak flow meters for scalable ASHA-led screening. This is a novel, low-cost adaptation for peripheral workers where specialist access is limited.​Unlike hospital/clinical-centric models, it integrates history-taking, risk assessment, and portable simple peak flow meter (15) portable spirometry at HWCs, close to the successful Kerala SWASS model, but tailored for CHO training for diagnosis at HWCs.​ (22)Feasibility metrics (yield, cost, acceptability) are uniquely strong in their use of a mixed-methods approach. Successful ***SHVASAN*** implementation can inform the NCD 2023 expansion and strengthen policy recommendations as public health services prepare for broader rollout in the near future.

Limitations and Challenges: The generalizability of ***SHVASAN*** findings beyond Pune's rural PHCs hinges on multi-district scaling trials, as local dynamics may not fully translate across diverse Maharashtra contexts, such as tribal belts and coastal clusters. ASHA workload pressures in NHM settings pose a significant challenge, as community health workers often juggle multiple responsibilities alongside respiratory screening demands. Severe cases need referrals to a higher centre.

### Ethics and dissemination

#### Ethical considerations

The final study protocol, including the final version of the other essential documents, is approved by the Institutional Ethics Committee (DHR Reg. No: EC/New/INST/2022/MH/0150 – Ref No. BVDUMC/IEC/317/25-26). There is no risk involved in conducting the study. Written informed consent will be taken before voluntary participation in the study. The PEFR and spirometry procedures will be explained at the time of the tests and performed as per NPCDCS 2021 guidelines. Anonymity and confidentiality will be maintained throughout the study, using study identifiers by assigning participant codes.

### Dissemination

Sharing with policy shapers and makers
Preparing action-oriented policy briefs that may highlight key findings, implications, and specific recommendations tailored to national, state, or district-level decision-makers.Engage with policymakers early and throughout the study (e.g., formal meetings, consultative meetings) and present findings through trainings/ technical briefingsFeeding back results to the community
Organise community dissemination sessions (village meetings, or stakeholder conclaves) using local language, to explain what the study foundPresenting at scientific conferences
Submit abstracts and present findings at national and international conferences to share methods, preliminary or final results, and lessons learned with other researchers.Publishing in peer-reviewed journals-
Papers on study design, methods, major findings, or implementation experience, and submit them to relevant peer-reviewed journals in public health, respiratory medicine, or primary care
